### Outcome and assessments

The primary study outcome was the SRI questionnaire, a 49-item questionnaire specifically designed for chronic respiratory failure patients with home mechanical ventilation. The domain scores are calculated by transforming the mean item score into a percentage ranging from 0 (worst quality of life) to 100 (best quality of life) [29, 30]. SRI questionnaire could not be an outcome but the score of SRI questionnaire.

Secondary outcomes were compliance with the ventilator, change in arterial PaCO2 and PaO2, change in lung function, time to readmission or death within 12 months from any cause, all-cause mortality, exacerbation and hospitalization frequency, safety analysis, cost-effectiveness analysis, and other health-related quality of life, measured by the modified Medical Research Council score (MRC) [31] to assess dyspnea (0 = no dyspnea, 4 = dyspnea at rest), the COPD assessment test (CAT) [32, 33], and COPD nocturnal symptom assessment test (cNAT).

Adherence with the ventilator was observed by monitoring the daily usage, usage days, ventilator settings, and other parameters in the IOT platform. Arterial blood gas analysis was taken during the daytime at rest without oxygen or ventilatory support unless patients were unable to stop ventilatory support even for short periods. Lung function was assessed according to national guidelines [28], including FEV1, FEV1% predicted, FVC, FVC % predicted, FEV1/FVC, total lung capacity, and residual volume. Hospital readmission and survival status of study patients were collected by checking medical records from the hospital or the general practitioner at each follow-up visit. For patients lost to clinical follow-up, each study center collected data from the national population register.

Occurrence time, severity, duration, adopted measure, and outcome of the adverse event occurring during the study should be recorded in the adverse events form according to the actual circumstances (Additional file 2). The common adverse events included facial rash, nasal ulceration, dry eyes, conjunctivitis, nasal stuffiness, nosebleed, gastric distension and device/mask intolerance [11, 17]. Serious adverse events were life-threatening, result in death, persistent, and significant disability, or incapacity, or make the participants’ hospitalization.

The main end-point in the cost-effectiveness analysis was cost per admission avoided. The direct and indirect costs included (1) healthcare costs for all hospital readmission; (2) healthcare costs for NIPPV-related medical equipment, such as the ventilatory; (3) healthcare costs for IOT medical equipment, such as tele-monitoring equipment and IOT platform; and (4)healthcare costs for IOT management, such as caregiver the time spent with the patient to initiate, titrate and adapt the NIPPV during the set-up and during the follow-up, maintenance, and support costs.

### Data management and quality control

At each study center, researchers added patient information to a dedicated pseudonymous paper case report form promptly and synchronously with input into the electronic case report form stored in locked file cabinets in areas with limited access. A coordinating and data monitoring committee has been established to record the occurrence of unexpected problems and to store, monitor, and manage the integrity, security, and authenticity of data. All members in the committee were independent of the study funders and declared no competing interests. The committee made safety and progress reports every week. Protocol amendments and the interim analyses would be decided based on the consultation.

### Sample size calculation and statistical analysis

The sample size was based on previous trials [7, 9, 10], assuming that SRI mean score was about 50 in usual NIPPV care after 1 year of treatment. We defined a non-inferiority margin of 5 for the difference in SRI mean score between the two groups, as the difference was found in previous researches about the effect of NIPPV with oxygen therapy vs oxygen therapy alone [9, 10]. On the assumption of a Standard Deviation (SD) of 20 [27] and a loss to follow-up of 25%, a sample size of 100 participants per group was needed to detect a difference of at least 5 between groups with a one-sided alpha of 0.025 and a beta of 0.1.

Continuous variables will be presented as mean and SD for normally distributed data or median and interquartile range (IQR) for nonnormally distributed data. Categorical variables will be presented as absolute numbers and percentages. Differences in continuous variables between two groups will be tested with the Student *t* tests or Mann–Whitney *U* test as appropriate.

The categorical variables will be compared by chi-square tests or Fisher’s exact tests as appropriate. We will use a general linear repeated measures analysis of variance with a Bonferroni correction or a paired t-test to analyze assessments changes within a group over time. The primary and appropriate secondary outcome analyses, such as compliance with the ventilator, change in arterial PaCO2 and lung function, will be performed including all randomized patients according to the intention-to-treat (ITT) principle. Missing data will be handled using the “last observation carried forward” method. We will use a linear mixed model to analyze the mean difference between the groups. When the conditions for use of the linear mixed model are not appropriate, a generalized estimating equation with correction for the baseline value and minimization variables (age, body mass index, frequency of COPD readmissions over 12 months) will be used. Time from randomization to death will be performed according to the ITT principle using the Kaplan–Meier approach and the log rank test. Hazard rate will be analyzed using a Cox proportional hazards regression model adjusted for minimization covariance. When the conditions for use of are not appropriate, the time-dependent cox regression model will be used. Safety analyses will be performed on all randomized patients. Additionally, per-protocol analyses of all outcomes will be analyzed as a sensitivity analysis, including patients finishing the study according to the protocol.

Two-sided P values less than 0.05 will be considered to be statistically significant. Statistical analyses will be performed using SPSS software (version 25.0, IBM SPSS).

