**Methods:**

This multicenter, prospective, randomized controlled trial was conducted with a total of 200 COPD patients with chronic hypercapnic respiratory failure. Using a computer-generated randomization process, patients were randomized (in a 1:1 ratio) into the usual NIPPV (control group) or to receive additional IOT-based management (intervention group) for 12 months. The primary outcome was the Severe Respiratory Insufficiency (SRI) questionnaire. Secondary outcomes included compliance with the ventilator, gas exchange, lung function, health-related quality of life, hospitalization frequency, time to death within 1-year, all-cause mortality, safety analysis, and cost-effectiveness analysis.

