## Background

Home non-invasive positive pressure ventilation (NIPPV) has long been undetermined in patients with stable chronic obstructive pulmonary disease (COPD) with chronic hypercapnic respiratory failure (CHRF) [1–7]. Previous research yielded conflicting results on survival, re-hospitalization, lung function, gas exchange, exercise tolerance, and quality of life [3–8]. However, recent randomized controlled trials have indicated that high-intensity NIPPV, which used high levels of inspiratory positive airway pressure (IPAP) with a high backup respiratory rate aimed at maximal PaCO2 reduction, showed physiological and clinical benefits [9, 10]. On the basis of these positive results, a recent meta-analysis demonstrated that home NIPPV was associated with a lower risk of mortality and all-cause re-hospitalization compared with no device support, but no significant difference in quality of life had been identified [11]. NIPPV has become evidence-based care for stable hypercapnic COPD patients [12–14].

There are still other challenges including appropriate follow-up, telemonitor, and management to ensure treatment effectiveness, adherence, and security and to improve quality of life. Usually, hospitals prescribe NIPPV, companies sold the ventilator while patients have little information of knowing how to use and maintain NIPPV at home [15, 16]. In fact, actively monitoring, communicating information, and solving problems during follow-up were crucial for long-term adherence and clinical outcomes [1, 16–18]. Furthermore, home NIPPV can be considered not only as a treatment, but also as a tele-monitoring predictor of objectively detecting acute exacerbations of COPD onset [16, 18]. However, the increasing number and costs of ventilator-dependent individuals make health providers largely insufficient to face the demands.

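### The 5-point SRI non-inferiority margin is set equal to the cited effect of NIPPV itself, with no discount, and does not fit the stated primary aim

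*Protocol article*

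**What the plan says.** The section Sample size calculation and statistical analysis states: "We defined a non-inferiority margin of 5 for the difference in SRI mean score between the two groups". The reason follows in the same sentence: "as the difference was found in previous researches about the effect of NIPPV with oxygen therapy vs oxygen therapy alone". No other basis for the figure is offered.

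The planning inputs are a usual-care mean of about 50, an SD of 20, 25% loss to follow-up, one-sided alpha 0.025 and beta 0.1. The stated result is "a sample size of 100 participants per group was needed to detect a difference of at least 5 between groups".

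Four other places bear on the point:

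- **Abstract, Methods:** patients are randomized to usual NIPPV "or to receive additional IOT-based management (intervention group) for 12 months". The Intervention section confirms that both arms receive NIPPV with the same in-hospital titration, so IOT management is an add-on.
- **Background, aims:** quality of life belongs to the primary effectiveness aim. Non-inferiority appears only in the secondary aim, for PaCO2, mortality and all-cause readmission.
- **Background, evidence:** a meta-analysis of home NIPPV against no device found benefits on mortality and re-hospitalization, "but no significant difference in quality of life had been identified".
- **End of the statistical section:** significance is declared at a two-sided P below 0.05, and the between-group mean difference is to be estimated with a linear mixed model.

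**The concern.** A non-inferiority margin is the largest deficit that would still count as acceptable. When it is anchored to the effect of an established treatment, it is normally set below that effect, so that success shows some of the effect's size has been kept. Here the margin is the anchor itself, undiscounted.

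The document also gives no reason to accept any deficit on SRI. IOT management is added to the same NIPPV and is meant to improve quality of life. Lower cost is hoped for, but the sample size section does not link it to a tolerated SRI loss.

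At stake is what a success claim on the primary outcome would mean. A claim of non-inferiority on SRI would leave open a deficit that, on the sponsor's own yardstick, is about as large as the gain from adding NIPPV to oxygen.

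**Working it through.** **Inputs**, all from the sample size section: margin 5; historical difference 5 (the document equates the two); SD 20; one-sided alpha 0.025; power 90%; 25% loss; 100 per group. Allocation is 1:1. (1.960 + 1.282)² = 10.507.

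**1. The plan's own sample size.** With a true difference of 0:

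n per group = 2 × 10.507 × 20² / 5² = 336.2, so 337 evaluable. With 25% loss, 337 / 0.75 = 449.3, so 450.

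The stated 100 per group is not reproduced. Assuming a true 5-point advantage for IOT, which the document does not state, gives 2 × 10.507 × 400 / 10² = 84.1, so 85 evaluable and 114 with loss. That also misses 100. The sample size is a separate error; it matters here because it limits what any replacement hypothesis can deliver.

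**2. Margin against its anchor.** 5 / 5 = 100%, so the required preserved fraction is 0%. Non-inferiority is met when the lower 95% limit for IOT minus usual care lies above −5. The interval may therefore reach almost to the full 5 points. If the true NIPPV effect is below 5, the margin exceeds it.

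**3. What passing would require at this size.** The CI half-width is 1.96 × 20 × √(2/n).

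| Evaluable per group | Half-width | Observed difference needed (−5 + half-width) |
|---|---|---|
| 75 | 6.40 | above +1.40 |
| 100 | 5.54 | above +0.54 |

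**4. Power for a 5-point difference.** Power = Φ(5 / (20√(2/n)) − 1.96).

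- 75 per group: SE = 3.266; 5/3.266 = 1.531; Φ(−0.429) = 33%.
- 100 per group: SE = 2.828; 5/2.828 = 1.768; Φ(−0.192) = 42%.

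These figures apply both to non-inferiority at a true difference of 0 and to superiority at a true difference of 5. Changing the label does not change the power.

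**5. A margin smaller than the effect.** The document gives no preserved fraction, so these are illustrations (true difference 0, SD 20, 90% power):

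| Fraction preserved (assumed) | Margin | Evaluable per group | With 25% loss |
|---|---|---|---|
| One quarter | 3.75 | 2 × 10.507 × 400 / 14.06 → 598 | 798 |
| One half | 2.50 | 2 × 10.507 × 400 / 6.25 → 1,345 | 1,794 |

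**The case against.** The strongest reply is that the preserved-fraction argument was built for a new treatment that replaces an active control. Here nothing is replaced, so NIPPV's benefit is not given up. That stands as a limit on the wording: a 5-point deficit would only match the NIPPV effect in size. It does not rescue the margin, because the sponsor chose that effect as the yardstick.

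A reader might infer that a non-inferior result is compatible with losing the whole benefit of NIPPV. The document does not support that as a general statement. Both arms keep NIPPV, and success at 5 excludes a deficit of 5 or more. Almost as large is exact if the effect is 5; as large or larger applies only if the effect is smaller.

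A reader might also infer that the primary result would be uninterpretable. It would not be: the mixed-model estimate and its interval can be read whatever the margin. Only the non-inferiority label would mislead.

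Two further replies stand in part. The 5-point historical effect is read from one loosely worded sentence, and the cited trials were not checked. And at the assumed SD, passing would need a point estimate slightly in favour of IOT. That protection comes from low precision and would disappear with a smaller SD.

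Finally, net cost is itself under test, so one cannot say that IOT simply adds cost. Savings could in principle justify a non-inferiority frame, but the document does not make that argument for SRI.

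**Conclusion.** The concern holds in this form: the SRI margin equals the full NIPPV effect as the document describes it, with no discount or other justification. It also sits badly with the primary aim, with the sample size sentence about detecting a difference, and with a listing of non-inferiority aims that leaves out SRI. The two-sided 0.05 level fits superiority more naturally, although it does not by itself contradict a one-sided 0.025 non-inferiority test.

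The ratio of 100% rests on the document's own equation of the two differences. The Background's report of no significant quality-of-life difference makes an effect below 5 possible; it does not establish one. The power figures rest on SD 20 and an unadjusted comparison. Baseline adjustment could help, but 90% power with 75 per group would need an effective SD of about 9.4 (5 / (√(2/75) × 3.2415)). The 2.5-point figure is a convention, not a ceiling found in the document.

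**What to change.** 1. Remove 5 points as a non-inferiority margin for SRI.
2. State the primary comparison as superiority of NIPPV plus IOT over NIPPV alone on the SRI score, with 5 points as the target difference, tested at two-sided 0.05. Report the estimate with its 95% CI.
3. Disclose that at SD 20 this target needs about 337 evaluable per group (about 450 with 25% loss), and that 100 per group gives about 33% power with 75 evaluable and 42% with all 100.
4. If a non-inferiority statement on SRI is kept, justify a margin smaller than the NIPPV effect, and state that 200 patients are not expected to meet it.

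The edit is short, but it redefines the primary hypothesis. Trial status describes recruitment as ongoing, so it should be a dated amendment made before anyone sees outcome data by arm. The cost is that non-inferior on SRI is no longer available as a success claim, and that the low power becomes explicit. Superiority does not cure the sample size.

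### The stated inputs need about 450 patients per group, not 100; as planned, power for 5 SRI points is about 33%, not 90%

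*Protocol article*

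**What the plan says.** Everything needed is in one paragraph of the Protocol article (Methods, Sample size calculation and statistical analysis).

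- Control-group level: "assuming that SRI mean score was about 50 in usual NIPPV care after 1 year of treatment".
- Margin: "We defined a non-inferiority margin of 5 for the difference in SRI mean score between the two groups".
- Variability and attrition: "On the assumption of a Standard Deviation (SD) of 20 [27] and a loss to follow-up of 25" per cent.
- Error rates: "with a one-sided alpha of 0.025 and a beta of 0.1".
- Result: "a sample size of 100 participants per group was needed to detect a difference of at least 5 between groups".

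The Study design and patients section confirms 200 patients allocated 1:1. The last paragraph of the statistical section sets significance at two-sided 0.05, which has the same critical value as one-sided 0.025. The paragraph states no assumed true difference alongside the margin, no baseline correlation and no other variance reduction.

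**The concern.** A 5-point difference with an SD of 20 is a standardised effect of 0.25. Ninety per cent power for an effect that small needs several hundred patients per group, so 100 per group, with a quarter of them expected to be lost, looks far too few.

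This is the calculation for the primary outcome. If the 90% is wrong, a non-significant result could be taken as good evidence that the two forms of management do not differ, or a failed non-inferiority test as evidence of harm, when the trial was simply too imprecise to tell.

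**Working it through.** **Inputs** (all from the sample size paragraph): difference or margin Δ = 5; SD σ = 20; one-sided α = 0.025, so z = 1.960; β = 0.1, so z = 1.282; loss 25%; 1:1 allocation. The control mean of 50 does not enter the formula.

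**1. Attempt to reproduce 100 per group**

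n per group = 2 × (1.960 + 1.282)² × σ² / Δ² = 2 × (3.2415)² × 400 / 25 = 336.2, so 337 evaluable.

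Allowing for loss: 336.2 / 0.75 = 448.3, so 449 randomised per group (450 if 337 is divided by 0.75). Multiplying by 1.25 instead gives 422. None of these is 100.

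For non-inferiority with margin 5 and true difference 0, the formula and the answer are identical.

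**2. Other settings, keeping Δ = 5 and σ = 20**

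| One-sided α | Power | Evaluable per group | Randomised per group (÷ 0.75) |
|---|---|---|---|
| 0.025 | 90% | 337 | 450 |
| 0.05 | 90% | 275 | 367 |
| 0.025 | 80% | 252 | 336 |
| 0.05 | 80% | 198 | 264 |
| 0.10 | 80% | 145 | 194 |

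Even the most lenient row needs nearly twice the stated number.

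**3. Power and precision of the planned trial**

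| | 75 evaluable per group | 100 per group, no loss |
|---|---|---|
| Standard error = 20 × √(2/n) | 3.266 | 2.828 |
| Power = Φ(5/SE − 1.960) | Φ(1.531 − 1.960) = 33.4% | Φ(1.768 − 1.960) = 42.4% |
| t-based power | 33.0% | 42.0% |
| 95% CI half-width = 1.960 × SE | 6.4 | 5.5 |
| Observed advantage needed to exclude −5 | 6.4 − 5 = 1.4 | 5.5 − 5 = 0.5 |
| Difference detectable with 90% power = 3.2415 × SE | 10.6 | 9.2 |

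**4. What would make 100 per group correct**

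With 75 evaluable per group and 90% power, one of these must hold:

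- SD = 5 / (3.2415 × √(2/75)) = 9.4, less than half the stated 20; or
- a difference of 10.6 points, about twice the stated 5; or
- a baseline-to-12-month correlation of √(1 − (9.45/20)²) = 0.88, used in a baseline-adjusted analysis.

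The paragraph states none of them. An SD of 10, or a difference of 10, comes close but gives 84.06 / 0.75 = 112.1, so 113 randomised per group (114 if 84.06 is first rounded up to 85).

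**The case against.** The strongest defence takes both of the paragraph's statements together: a non-inferiority margin of 5 and a true advantage of 5 for the intervention. The distance to the margin is then 10 points. That needs 85 evaluable per group, or 107 to 114 randomised depending on how loss is applied. Power is Φ(10/3.266 − 1.960) = 86.5% with 75 evaluable, and 94% if all 100 were fully observed. This is the only reading that comes near the stated number, and it shows that the 33% depends on the hypothesis. But the article never says that a true benefit is assumed within a non-inferiority test, and after the 25% loss even this reading reaches neither 100 per group nor 90% power.

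A second defence is that the primary analysis includes all randomised patients, with the last observation carried forward, so 100 per group would nominally be analysed. Carrying values forward does not restore the lost information. Even granting it in full, power is 42% and the interval is still wider than the margin on either side of zero.

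A third is that the planned linear mixed model, or adjustment for baseline, would cut the variance. The documents give no correlation. For assumed values of 0.5 to 0.7, treating the analysis as a single 12-month comparison, power is 42% to 57% with 75 per group and 53% to 70% with 100. The gain is real but well short of 90%, and the plan does not claim it.

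What stands from these points is a qualification. An inconclusive result is the likelier outcome if the true difference is 0 under non-inferiority or 5 under superiority. It is not the likelier outcome if non-inferiority is tested and the intervention is truly 5 points better.

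**Conclusion.** The sample size is wrong on its own inputs. The required number is 337 evaluable and about 450 randomised per group, against 100 stated. Power is about 33%, some 57 percentage points below the claim, and no more than about 42% if nobody is lost.

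These figures rest on the stated SD of 20, an unadjusted comparison of two means, and either a true difference of 5 tested for superiority or a true difference of 0 tested against a margin of 5. No reading that the article actually states yields 100 per group. This must be corrected, because it misstates what the trial can show on its primary outcome. It is not a detail left to an analysis plan: the article gives both the inputs and the result, and they disagree.

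**What to change.** Rewrite the sample size paragraph, leaving enrolment unchanged:

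1. Say whether the primary comparison is superiority or non-inferiority and, if non-inferiority, what true difference is assumed.
2. Replace the 90% claim with the power and precision that the numbers support. For example:

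> With 200 patients randomised, 25% loss to follow-up and an SD of 20, the trial has about 33% power for a true difference of 5 SRI points in a superiority comparison (equally, for non-inferiority with a margin of 5 and no true difference). It has 90% power to detect a difference of 10.6 points. The expected 95% confidence interval half-width is 6.4 points.

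3. If the SD in the original calculation was another quantity, such as the SD of change or a residual SD after baseline adjustment, state it and its source. A value of about 9.4 reproduces 100 per group.
4. Commit to interpreting the primary result through its confidence interval, so that a non-significant difference or a failed non-inferiority test is not read as a definite answer.

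The cost is wording, plus a stated power much less favourable than the present one. Recruitment was due to finish in January 2022 according to the Trial status section, and the correction does not call for more patients.

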**Fig. 3 Fig3:**
[figure not shown]
The study flow diagram. NIPPV, noninvasive positive pressure ventilation; COPD, chronic obstructive pulmonary disease; IOT, Internet of things; CHRF, chronic hypercapnic respiratory failure

The enrolled patients who are lost to follow-up, suffered serious adverse events, withdraw consent, or met endpoints will be regarded as a withdrawal. The Intervention and follow-up was terminated If one of the endpoints occurs: (1) death; (2) did not receive intervention as randomized; (3) the need for endotracheal intubation and invasive ventilation during exacerbation; (4) pneumothorax; (5) had active unstable coronary artery syndrome or cerebrovascular disease; (6) unable to tolerate noninvasive ventilation due to surgery and so on; and (7) cognitive impairment or unstable psychiatric morbidity.

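### Last observation carried forward is fixed for the primary and named secondary analyses beside a mixed model that does not need it; the bias can go either way and can favour non-inferiority

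*Protocol article*

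**What the plan says.** All statements are in the Methods of the protocol article.

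- **Analysis set** (Sample size calculation and statistical analysis). The primary analysis and the suitable secondary ones "will be performed including all randomized patients according to the intention-to-treat (ITT) principle". Ventilator use, PaCO2 and lung function are the secondary outcomes named as examples.
- **Missing data** (same paragraph). "Missing data will be handled using the “last observation carried forward” method". No outcome and no reason for missingness is excepted.
- **Model** (the next sentence). "We will use a linear mixed model to analyze the mean difference between the groups". A generalized estimating equation is the fallback.
- **Expected loss** (sample size paragraph). The calculation allows for "a loss to follow-up of 25" per cent.
- **End of follow-up** (Follow-up and endpoints, text after Fig. 3). "The Intervention and follow-up was terminated If one of the endpoints occurs: (1) death; (2) did not receive intervention as randomized". The list continues with intubation, pneumothorax and being "unable to tolerate noninvasive ventilation due to surgery and so on", among others.
- **Sensitivity analysis**. The only one named is that "per-protocol analyses of all outcomes will be analyzed as a sensitivity analysis, including patients finishing the study according to the protocol".
- **Visits** (Table 1). SRI, blood gases and compliance are scheduled at baseline and at 3, 6 and 12 months; lung function only at baseline and 12 months.

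**The concern.** A linear mixed model estimates the 12-month difference from every observed visit and is valid if data are missing at random. Filling the gaps first gives up that property. It substitutes the assumption that each patient's score stays at its last value.

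That assumption is weak here. Patients are identified during an admission for exacerbation, after stabilisation, so early values may represent month 12 poorly. The events that end follow-up are mostly bad outcomes. For lung function there is no intermediate visit, so every dropout is assigned exactly zero change.

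The sample size paragraph sets a non-inferiority margin of 5 SRI points. In a non-inferiority comparison, a method that shrinks a true deficit makes a false claim more likely. If the comparison is instead read as one of superiority, the same shrinkage costs power.

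**Working it through.** The plan gives no figure of its own for the effect of this rule, so there is none to reproduce. The 100 per group is taken as given; whether it follows from its stated inputs is a separate question.

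**Inputs from the document:** margin 5, SD 20, loss 25%, 100 per group, one-sided alpha 0.025, visits at 0, 3, 6 and 12 months.

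**Assumed, because the document is silent:** timing of dropout, dropout by arm, course of the SRI score, within-patient correlation (0.6 or 0.7) and hours of use.

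**1. Expected 12-month difference under carry-forward.** It is the completers' share times the 12-month difference, plus the sum over last visits of (share leaving × difference at that visit). Take a deficit of 0, 1.25, 2.5 and 5 points at months 0, 3, 6 and 12, with 25% dropout in both arms:

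- Last visits spread evenly: 0.75 × 5 + (0.25/3) × (0 + 1.25 + 2.5) = 3.75 + 0.31 = 4.06.
- All leave after baseline: 0.75 × 5 + 0.25 × 0 = 3.75.
- All leave after month 6: 0.75 × 5 + 0.25 × 2.5 = 4.38.

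The attenuation is 12–25%.

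**2. False non-inferiority when the true deficit equals the margin** (lower 95% limit above −5, 100 per arm, evenly spread dropout):

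| Analysis | Mean estimate | False non-inferiority |
|---|---|---|
| Baseline-adjusted, correlation 0.6, no dropout | – | 2.9% |
| Same, 25% dropout, carried forward | −4.06 | 6.5% |
| Same, 40% dropout, carried forward | −3.48 | 10.4% |
| Unadjusted, correlation 0.7, completers only | −5.00 | 2.8% |
| Same, 25% dropout, carried forward | −4.04 | 5.6% |

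Hand check of the 6.5%: the shift is 5 − 4.06 = 0.94 and the standard error in that simulation is 2.20. The critical value falls to 1.96 − 0.94/2.20 = 1.53, and a standard normal variable exceeds 1.53 about 6.3% of the time.

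**3. Other courses, same baseline-adjusted set-up:**

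- Full deficit of 5 from month 3: 0.75 × 5 + (0.25/3) × (0 + 5 + 5) = 4.58; false non-inferiority 4.1%.
- Deficit of 7, 6 and 5 at months 3, 6 and 12: 3.75 + (0.25/3) × 13 = 4.83; 3.2%.
- Both arms decline 10 points, dropout 30% control and 20% intervention, deficit 5: estimate −4.94; 2.8%.

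**4. No true difference at 12 months:**

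- Both arms run 50, 47.5, 45, 40; dropout 35% control, 15% intervention. Control: 0.65 × 40 + (0.35/3) × 142.5 = 42.625. Intervention: 0.85 × 40 + (0.15/3) × 142.5 = 41.125. False difference −1.5.
- Both arms run 45, 47, 48, 50 with the same dropout. Control: 32.5 + (0.35/3) × 140 = 48.83. Intervention: 42.5 + (0.15/3) × 140 = 49.5. False difference +0.67, or −0.67 if the dropout rates are swapped.
- Intervention 5 points better at months 3 and 6 only, equal dropout of 25%: (0.25/3) × (0 + 5 + 5) = +0.83.

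**5. Compliance.** Suppose users average 6 h/day and 20% of control and 5% of intervention patients stop. The true difference is 6 × 0.95 − 6 × 0.80 = 0.9 h/day. If pre-stopping hours are carried forward, it is 0. With equal stopping in both arms the error cancels.

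**The case against.** Several stronger readings are tempting, and the document does not support them.

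- **Bias always towards no difference.** This holds for equal dropout with a growing difference. Steps 3 and 4 show courses with little inflation and courses with a false difference of either sign. The 5.6–6.5% is one scenario, not a forecast.
- **Standard error too small.** This was not demonstrated. In the baseline-adjusted simulation the mean model standard error and the empirical SD of the estimate were both 2.20, so the test is calibrated for what carry-forward estimates. That is smaller than the completers' 2.62, but the false claims come from the shift in the estimate.
- **Dead patients are given living scores.** The article never says that SRI after death counts as missing; this is an inference from an unqualified rule. A mixed model under missing-at-random does not settle it either, since it too implies a 12-month course for patients who died. Scoring death as 0 is a choice of estimand: the article defines 0 as the worst quality of life, not as death.
- **Deaths go unpenalised.** All-cause mortality and time to readmission or death are secondary outcomes, vital status is sought from the population register, and time to death is analysed by intention to treat. Deaths are compared, though not within the SRI analysis.
- **Stopped users keep their old hours.** Use is recorded through the platform, so a patient who stops but stays connected has observed zeros. Carry-forward arises only where monitoring ends.

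It is also fair that the per-protocol analysis largely avoids carried-forward values. But it does so by dropping the patients who left, so it has its own selection and does not test the missing-data assumption. Further sensitivity analyses may stand in an analysis plan that is not shown. The carry-forward rule itself is stated in the article, so it is not a detail left open.

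**Conclusion.** The point stands in limited form. The plan fixes carry-forward for the primary and named secondary analyses, next to a model that makes it unnecessary, in a trial where a quarter of patients are expected to be lost and follow-up ends at informative events. Following the plan as written can bias the result, in a direction that cannot be known beforehand.

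The size depends on assumptions. For non-inferiority at the margin of 5, the error rate is roughly doubled if a deficit builds linearly and dropout is equal, and modestly raised or nearly unchanged under the other courses examined. With no true difference, false differences of −1.5 to +0.83 points appeared. For lung function no scenario is needed: every dropout with a baseline value only is assigned zero change. Because the rule governs the primary conclusion, it should be changed before analysis.

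**What to change.** 1. Delete the carry-forward sentence. Fit the planned linear mixed model to all observed 3-, 6- and 12-month SRI scores with adjustment for baseline, and name missing-at-random as its assumption.
2. Add two sensitivity analyses: delta-adjusted multiple imputation, and one that handles death explicitly, for example by assigning the worst SRI value. The second is needed because the mixed model alone does not address death.
3. For compliance, count days alive after ventilation is known to have stopped as 0 hours, and do not carry earlier use forward.

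The cost is analysis wording and two extra analyses, with a somewhat wider confidence interval than under carry-forward. No new data are required.
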